### Participants

A total of 30 patients with CNLBP and 15 demographically matched asymptomatic (healthy) participants will be recruited for COSCIOUS. The sample size of CNLBP patients is determined based on previous studies that have evaluated the effect of lumbar extension exercise on the kinematics of the lumbar spine and hips during a common daily activity [25,26]. Steele et al [26] calculated the sample size for their study and reported that a minimum of 7 participants would be required in each group to achieve 80% power at an alpha level of *P* ≤.05 [26]. Therefore, 45 participants will be divided into 3 groups: 2 experimental groups (15 patients with CNLBP in each group) and one healthy control group (15 asymptomatic participants). Considering some attrition, the sample size was increased to 15 participants in each group. The CNLBP patients will be identified and recruited by posters, emails, and word of mouth from the university and the surrounding locality. Direct referral also will be provided from 2 orthopedic surgeons and 2 neurologists in Tehran. Inclusion criteria of COSCIOUS are as follows:

CNLBP (LBP persisting for more than 3 months in the absence of an underlying pathology)Aged between 18 and 40 yearsPain between 3 and 6 at rest on a 0- to 10-point pain visual analog scale (VAS), where 0 represents no pain and 10 is the worse pain imaginableAbility to perform STS movement and its reverse without an aidNo contraindication for exerciseNo obvious deformity of the spine, pelvis, and lower extremitiesNo autoimmune diseases (eg, rheumatoid arthritis) [12]No pregnancy

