### Statistical Analysis

Statistical analyses will be performed on a personal laptop using SPSS for Windows release version 21.0 (IBM Corp) and STATA version 13 (StataCorp LLC). The comparability of asymptomatic participants and CNLBP patients on disability level, pain intensity, and kinematic variables at baseline will be analyzed using the independent *t* tests for parametric and Wilcoxon test for nonparametric distribution. In addition, a mixed-model 2-way analysis of variance (ANOVA) for each dependent variable (disability level, pain intensity, maximum joints ROM, joint angular velocities, lumbar/hip motion ratios, and maximum and minimum relative phase differences), with the 2 factors being group (core stabilization/general exercise) and time (preintervention/postintervention). After intervention, comparison between core stabilization group, general exercise group, and asymptomatic participants will be made using the ANOVA test (*Scheffe* post hoc tests). In addition, an intention-to-treat analysis will be conducted if any protocol deviation is observed at the end of the study due to attrition or loss to follow-up. Perceived pain and functional disability will be compared with consensus standards for minimal clinically important change (MCIC) [48]. Ostelo et al [48] considered the MCIC for VAS as 15 mm and for RMDQ as 5 points for patients with LBP. Furthermore, effects sizes will be measured using the Cohen *d* [49]. Statistical significance level is set at *P* ≤.05.

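### Scheffe post hoc tests are valid but slightly inefficient for the three-group comparison if, as appears, only the three pairwise differences are wanted

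*Protocol article*

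**What the plan says.** The Statistical Analysis section of the protocol article contains three group analyses. Patients and asymptomatic participants are compared at baseline with t or Wilcoxon tests. The two exercise arms are compared over time with a mixed two-way ANOVA (group by time). After intervention, a "comparison between core stabilization group, general exercise group, and asymptomatic participants will be made using the ANOVA test", with Scheffe "post hoc tests". This point concerns only the third analysis.

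The section does not list the contrasts that the post hoc tests are to examine and gives no reason for choosing Scheffe. On the error level it says: "Statistical significance level is set at *P* ≤.05". On size, the Participants section says: "Considering some attrition, the sample size was increased to 15 participants in each group". The Procedure section adds that the asymptomatic group is assessed once, before the intervention, and takes no part in the second assessment.

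**The concern.** Scheffe's critical value protects every linear contrast among the group means, including weighted and pooled ones. Three groups give only three pairwise differences: core against general, core against asymptomatic, and general against asymptomatic. If those are all that is wanted, Scheffe pays for protection that the analysis does not use. Tukey's method is built for the set of all pairwise differences and holds the same nominal 5% family-wise level with a smaller critical value.

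At stake are the width of the reported intervals and the chance of detecting a pairwise difference in groups of 15, where precision is already modest. The plan can also give a significant ANOVA with no significant pair to explain it.

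**Working it through.** **Inputs from the protocol article.** Three groups of 15 (Participants), hence 45 − 3 = 42 error degrees of freedom without attrition. Alpha is 0.05 (Statistical Analysis), taken as two-sided because sidedness is not stated.

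**Assumptions.** No effect size, standard deviation or attrition rate is given. Power is therefore shown for standardised differences d from 0.8 to 1.5, and group size is varied from 7 to 15.

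**The plan's own figure.** The Participants section reports from a cited study that "a minimum of 7 participants would be required in each group to achieve 80% power at an alpha level of *P* ≤.05". Without an effect size this cannot be reproduced forward. Solved backward, 7 per group at 80% power implies a standardised difference of 1.63 (two-sided t), 1.41 (one-sided t) or 1.50 (normal approximation). None of these addresses the three-group comparison, so the plan has no figure of its own for this analysis.

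**Critical values for a pairwise difference.**
- Scheffe: √(2 × F(0.95; 2, 42)) = √(2 × 3.220) = 2.538.
- Tukey: q(0.95; 3, 42)/√2 = 3.436/√2 = 2.429.
- Bonferroni for three tests, for reference: 2.494. Even this is less strict than Scheffe here.
- Scheffe to Tukey: 2.538/2.429 = 1.045. Squared, this is 1.091, so the extra width corresponds to about 9% more participants.

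**Half-width of the simultaneous 95% interval**, critical value × √(2/15), in standard deviation units: 0.927 (Scheffe) against 0.887 (Tukey).

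**Actual family-wise error over the three pairs.** From the studentized range, Scheffe's is 3.9%. In 400,000 simulated trials with no true differences, the rates were 3.87% (Scheffe), 4.94% (Tukey) and 4.95% (overall F). No Scheffe pair was significant without a significant F. It follows that (4.95 − 3.87)/4.95 = 22% of the significant F tests had no significant Scheffe pair.

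**Power per pair**, from the noncentral t with 42 df and noncentrality d × √(15/2):

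| Assumed d | Scheffe | Tukey |
|---|---|---|
| 0.8 | 37% | 41% |
| 1.0 | 58% | 62% |
| 1.2 | 77% | 80% |
| 1.5 | 94% | 95% |

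The largest gap is 4.1 points, near d = 0.9. The difference detectable with 80% power is 1.24 SD with Scheffe and 1.20 SD with Tukey.

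**If Tukey is read only after a significant F.** Its family-wise error falls to 4.5%. Power depends on where the third mean lies: 39.9% to 40.7% at d = 0.8 (Scheffe 37%) and 60.8% to 61.9% at d = 1.0 (Scheffe 58%). The gain is smaller but remains.

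**Sensitivity to attrition.** With 7, 10, 12, 13 or 15 per group, the ratio of critical values stays at 1.045 after rounding in the third decimal (1.0445 to 1.0447), and Scheffe's actual family-wise error stays between 3.9% and 4.0%.

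**The case against.** The strongest reply is that nothing here is wrong. Scheffe controls the family-wise error, and the section contradicts nothing on this point. Scheffe also agrees with the overall F test named in the same sentence: no pair can be significant when F is not. Tukey lacks that property; in the simulation, 4.94% − 4.48% = 0.46% of null trials had a significant Tukey pair without a significant F. The protocol also thinks in pooled terms elsewhere. All patients together are compared with asymptomatic participants at baseline, and the Introduction hypothesises a benefit of exercise therapy as such. Both exercise groups combined against asymptomatic would be a natural follow-up, and Scheffe covers it.

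Much of this stands. The choice is valid, the loss is small, and the pairwise-only family is an inference, because the contrasts are not listed. What does not stand is that the plan needs Scheffe: it states no pooled contrast for this analysis and gives no other reason for the method.

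Two stronger readings should be resisted. A reader might infer that Scheffe brings no gain in error control and that the switch has no downside. It does give stricter control (3.9% against 5%), and with many kinematic variables and no stated adjustment across them, using the full 5% for each is a real, if minor, trade-off. A reader might also infer that the trial's power to compare the two exercise programmes is reduced. It is not: that effect is tested in the group-by-time mixed ANOVA, which does not use Scheffe.

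**Conclusion.** The point holds as a minor inefficiency. If the three pairwise differences are the intended family, Scheffe gives intervals about 4.5% wider than Tukey and up to about 4 points less power per pair at the same nominal 5% level, and it uses only about 3.9% of that 5%. The ratio of critical values hardly moves with attrition. The power figures rest on assumed effect sizes, because the article gives none. At the large effects implied by the cited sample size the gap shrinks: at d = 1.5 with 15 per group it is about 1 point.

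The documents do not support calling the test invalid, nor saying that the randomised comparison is weakened. The affected analysis is supplementary and includes a non-randomised group measured only before the intervention; changing the post hoc method leaves that limit on interpretation in place.

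**What to change.** In the Statistical Analysis section, replace Scheffe by Tukey for the three pairwise comparisons after intervention (Tukey-Kramer if attrition makes group sizes unequal), and report the simultaneous 95% intervals. State whether the pairs are read only after a significant F. If a non-pairwise contrast is intended, such as the pooled exercise groups against asymptomatic participants, keep Scheffe and name that contrast.

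The change is one sentence and needs no further data. Its price is that the full 5% per variable is used instead of about 3.9%, and that a pair may occasionally be significant when F is not. Reading Tukey only after a significant F removes the second effect, lowers the family-wise error to 4.5%, and keeps most of the gain.

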## Results

COSCIOUS should be completed in December 2017. The results of this study will be submitted to a peer-reviewed MEDLINE-indexed journal for publication and will be presented at national and international academic and clinical conferences.

## Discussion

### Overview

To the best of the authors’ knowledge, this is the first time an investigation will evaluate the effects of core stabilization exercise on the kinematics and joint coordination of the lumbar spine and hip during STS and its reverse in patients with CNLBP. STS movement and its reverse are important functions required for conducting activities of daily living. Previous study has shown that these skills would be impaired in acute LBP [12]. However, the effects of CNLBP on flexion and extension phases of STS and its reverse is not well known, and COSCIOUS aims to investigate this issue.

Physical therapy programs play a key role in multimodal treatment approaches for CNLBP [50]. Therapeutic exercise is one of the few clearly effective physical therapy treatments to relieve pain for adults with CNLBP [50,51]. The European guidelines for the management of CNLBP suggest supervised exercise therapy as a first-line treatment [52]. In this investigation, the effect of the 2 most common types of therapeutic exercises prescribed for patients with LBP will be evaluated on the kinematics and joint coordination of functionally important activities. To the best of authors’ knowledge, no published study has assessed the effect of exercise therapy on STS movement and its reverse. The main study question is whether core stabilization exercise programs are effective in improving kinematic variables during STS and its reverse in CNLBP. In addition, a comparison will be made between the results of the 2 therapeutic exercises on STS and its reverse. The results of COSCIOUS will provide some insight into the effects of CNLBP on lumbar spine–hip coordination of activities of daily living.

### Limitations

The main limitation of this study is that young and middle-aged CNLBP participants will be included, thereby, the generalizability is limited. In addition, some study participants may be lost to follow-up.

### Conclusion

COSCIOUS will evaluate the effects of core stabilization exercise on the kinematics and joint coordination of the lumbar spine and hip during STS and its reverse in patients with CNLBP. In addition, the effects of CNLBP on the STS and its reverse will be investigated.

## Appendix

Multimedia Appendix 1 Core stabilization and general exercise programs.

## Abbreviations

ANOVA: analysis of variance
ASIS: anterior superior iliac spine
CLBP: chronic low back pain
CNLBP: chronic nonspecific low back pain
COM: center of mass
CONSORT: Consolidated Standards of Reporting Trials
COSCIOUS: core stabilization exercise on the kinematics and joint coordination of the lumbar spine and hip during sit-to-stand and its reverse in patients with chronic nonspecific low back pain
LBP: low back pain
LH: left hip
MCIC: minimal clinically important change
PSIS: posterior superior iliac spine
QTM: Qualisys track manager
RH: right hip
RMDQ: Ronald-Morris Disability Questionnaire
ROM: range of motion
RPA: relative phase angle
STS: sit-to-stand
VAS: visual analog scale
